**Figure 2 figure2:**
[figure not shown]
Patient trajectories at the 3 different study sites of the ePATH intervention.

### Analysis

Descriptive statistics will be presented with measures of central tendency and dispersion, as well as frequencies or percentages. The effectiveness of the intervention will be evaluated separately for the 2 hypotheses. As the trial involves repeated measures of data, a linear mixed model will be used to analyze the primary and secondary outcome measures. For ordinal outcome variables, a generalized estimating equation will be employed. The latter model will be used to evaluate the effect of the intervention on UI and sexual health at 1, 3, 6, and 12 months. An interaction term will be introduced into the model to examine the heterogeneity effect. A generalized linear model will be employed for intraindividual analysis of log data within the intervention group to evaluate associations between endurance and adherence to PFMT and postoperative outcome over time. We will perform residual analyses to assess model assumptions and goodness of fit. Assumption of normality will be checked using skewness and normal probability plot when necessary. An intention-to-treat analysis will be performed for the data. Patterns of missing data and dropout will be examined and, if necessary, multiple imputation will be used on the basis of the nature of the missing data. All statistical tests will be carried out at the 5% significance level (2-sided).

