The aim of the third phase was to compare the effectiveness of a tailored eHealth- and mHealth-assisted self-management support as a complement to standard care, with standard care. Primary outcomes are postoperative adverse effects (ie, urinary and sexual bother and function) in men undergoing RP. The secondary outcomes are physical activity, patient activation, motivation, health literacy, and overall well-being, which may be associated with the primary outcomes and have a mediating or confounding effect on the intervention.

The hypotheses of the study are the following:

The ePATH self-management support system will have a greater effect than standard care on patient-reported outcomes of UI and sexual bother and function at 1, 3, 6, and 12 months after RP.The ePATH self-management support system will have a greater effect than standard care on (1) physical activity, (2) patient activation, (3) motivation, (4) health literacy, (5) overall health and well-being, and (6) endurance and adherence to self-care at 1, 3, 6, and 12 months after RP.

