### Sample Size

Considering an effect size of 0.5 and a maximum of 4 domains (urinary, bowel, sexual, and hormonal) on the Expanded Prostate Cancer Index Composite with a 2-sided 5% significance level and a power of 80%, a sample size of 121 patients per group will be necessary given an anticipated dropout rate of 25% [43].

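### The sample size of 121 per group implies a 5% level split over four domains, but the Analysis section sets every test at 5% and gives no rule for several primary outcomes

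*Protocol article*

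**What the plan says.** The Sample Size section starts from "Considering an effect size of 0.5 and a maximum of 4 domains (urinary, bowel, sexual, and hormonal) on the Expanded Prostate Cancer Index Composite" and continues "with a 2-sided 5% significance level and a power of 80" per cent. It concludes that "a sample size of 121 patients per group will be necessary", with the dropout allowance expressed as "given an anticipated dropout rate of 25" per cent. The Abstract gives the total as 242.

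The first hypothesis, at the end of the Introduction, concerns "patient-reported outcomes of UI and sexual bother and function at 1, 3, 6, and 12 months after RP". Outcome Measures makes urinary and sexual bother and function primary. The bowel and hormonal domains appear there only as part of the questionnaire.

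The Analysis section plans a linear mixed model for repeated measures, with generalized estimating equations for ordinal outcomes, and again lists the four visits. It ends with "All statistical tests will be carried out at the 5% significance level (2-sided". The article contains no adjustment, no testing order, no single primary domain or visit, and no statement of which results would count as success.

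**The concern.** The number of domains is given as an input to the sample size. It has no role in a two-group comparison of means unless the significance level is divided by it. If it was divided, the trial is enrolling roughly 35 more men per group than an unsplit 5% requires, in order to control the error rate over four tests. The Analysis section, read as written, then tests each outcome at the full 5%, and that protection is not used.

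At stake is whether a claim on the primary outcomes carries a known error rate. This differs from a protocol that is silent on multiplicity and leaves it to the analysis plan. Here a level is stated for all tests, and it does not fit the trial's own sample size.

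**Working it through.** **Inputs (Sample Size section):** standardised effect d = 0.5, power 80%, two-sided 5%, 4 domains, dropout 25%, stated result 121 per group. Equal groups; the two-sample t-test is assumed, since no test is named.

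**1. Reproducing 121.** The normal approximation for completers per group is n = 2(z₁₋α/₂ + z₀.₈₀)² / d², and enrolment is n / (1 − 0.25).

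- α = 0.05: 8 × (1.960 + 0.842)² = 62.8, so 63, and 63 / 0.75 = 84.
- α = 0.05 / 4 = 0.0125: 8 × (2.498 + 0.842)² = 89.2, so 90, and 90 / 0.75 = 120.

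The t-test version, which is slightly larger:

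| Level per test | Completers per group | Divided by 0.75 |
|---|---|---|
| 0.05 (unsplit) | 63.77 | 85.0 (86 if 64 completers are used) |
| 0.025 (split over 2) | 77.31 | 103.1 |
| 0.0167 (split over 3) | 85.20 | 113.6 |
| 0.0127 (Sidak over 4) | 90.41 | 120.5 |
| 0.0125 (Bonferroni over 4) | 90.78 | 121.04 |
| 0.00625 (split over 8) | 104.18 | 138.9 |

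Other variants also miss, by the normal formula: one-sided 5% gives 67, 90% power at 5% gives 114, and 95% power at 5% gives 139. Only a split over four reaches 121. Bonferroni and Sidak cannot be told apart.

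**2. False-positive rate at 5% per test.** This is the chance of at least one significant primary result when there is no effect. With k independent tests it is 1 − 0.95ᵏ. For correlated tests it was simulated with 400,000 draws of correlated normal test statistics. The correlations are assumptions, as the article gives none.

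| Primary tests | Independent | Correlated |
|---|---|---|
| 2 domains, one overall test each | 1 − 0.95² = 9.75% | 8.3% at between-domain correlation 0.7 |
| 4 scores (bother and function separate), one test each | 1 − 0.95⁴ = 18.5% | 13.1% at correlation 0.7 |
| 2 domains × 4 visits | 1 − 0.95⁸ = 33.7% | about 20-28% at 0.2-0.5 between domains and 0.5-0.8 between visits |

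**3. What the planned size supports.** Completers: 121 × 0.75 = 90.75 per group. Power per test by t-test at d = 0.5 is 91.8% at 0.05, 86.5% at 0.025 and 80.0% at 0.0125.

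**4. Splitting the level is not enough without fixing the number of tests.** Four tests at 0.0125 give at most 4 × 0.0125 = 5%. Two domains at four visits, each at 0.0125, would give 1 − 0.9875⁸ = 9.6% if independent.

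**The case against.** **The conflict is inferred.** Both sections write 5%; neither 1.25% nor any correction is named. If the Sample Size section uses 5% for an overall level shared over four domains, the Analysis section may do the same. This stands in part. A reader might infer that the protocol prescribes Bonferroni at 1.25%, and the text does not say so. But the domain count has no other use in the calculation, and a sentence about all tests being carried out at 5% reads as a per-test level. If an overall 5% was meant, it still has to be written.

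**The match depends on rounding.** Rounding 90.78 up to 91 first gives 121.3, which rounds up to 122. The exact level is therefore uncertain, but no unsplit level comes near 121.

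**The inflation depends on choices that the article does not make.** A reader might count four domains at four visits, or 1 − 0.95¹⁶ = 56%. The documents do not support that as a primary error rate, because the bowel and hormonal domains are not primary. Nor is 34% an established figure. A mixed model allows one overall test per outcome, and the first hypothesis joins its outcomes and visits with "and". If every one had to be significant, the family-wise rate would not be inflated. No success rule is stated either way, so all the rates above hold only if any single significant result counts.

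**The choice of procedure belongs in the analysis plan.** Often true, and the absence of such detail is not the point here. The point is the stated blanket level that does not fit the sample size.

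**Conclusion.** The point holds in this form: 121 per group presupposes about 1.25% for each of four domains, while the Analysis section as written applies 5% to every test and gives no rule for the urinary and sexual outcomes at four visits. The 1.25% is an inference from the arithmetic, though a firm one.

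The size is conditional. Where any one significant primary test counts as success, every reading exceeds 5%: modestly with one overall test for each of two domains, and several-fold if each visit is a separate test. The correlated figures rest on assumed correlations. The documents do not show which reading is intended.

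**What to change.** Reconcile the hypotheses, Sample Size, Outcome Measures and Analysis sections, before outcome data are examined:

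- Name the primary EPIC-26 scales, and say whether bother and function are scored separately and whether the bowel and hormonal domains are primary.
- Test each primary scale once, either at one named visit or as one overall group effect over 1 to 12 months.
- For the primary tests, replace the blanket 5% with Bonferroni or Holm at an overall two-sided 5%: with Bonferroni, 0.0125 each if four scales are kept, 0.025 each if two.
- Report the other visits and all secondary outcomes as estimates with confidence intervals, labelled non-confirmatory.
- State in the Sample Size section which per-test level produced 121.

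This costs a few sentences and no patients. The trade-off is power per test: about 80% at 0.0125 or 86.5% at 0.025, against about 92% at an unadjusted 5%. The 80% at 0.0125 is the power that the sample size already promises.

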### Intervention Fidelity

To enable research to be implemented into clinical practice, it is important to report both internal and external contextual details on how the intervention has evolved during the research process. It is rare that a protocol for a randomized controlled trial is followed faithfully when delivering interventions outside laboratories or similar controlled environments. Therefore, it is necessary with flexible interventions that can be adapted to the target group and the unique circumstances of each clinical setting [57]. To describe those aspects as thoroughly as possible, we will follow the Template for Intervention Description and Replication checklist [58] (Table 2). We will carefully evaluate the intervention and its use to strengthen external validity through interviews with patients, retrieving log data from the ePATH app, and dropout analysis. We will also keep in close contact with the test clinics by phone, email, and visits throughout the study to make any necessary adaptions and modifications. All adjustments and contextual factors at the management level at the 3 study sites that may account for variations in implementation outcome will be documented and evaluated.


Patients’ usage of the ePATH self-management support system will be determined through extraction from the data logs to study user interactions with the different modules in the ePATH. Logistic regression will be performed to identify patterns of use, that is, associations between system use and patient characteristics. Such information is crucial in adapting the eHealth service to different patient groups.

Semistructured patient interviews will be conducted with a subsample of patients in the intervention group to provide deeper insight into how ePATH may support and promote adherence to self-care, strengthen patient health literacy, motivation, and the competences needed to manage self-care. We will also explore hindrances to self-care activities such as distress, anxiety, or insufficient or lack of support. Given the importance of understanding factors contributing to attrition, we will also interview patients who did not actively adapt to the ePATH. All interviews will be audio-recorded, transcribed verbatim, and analyzed using qualitative content analysis. These actions strengthen the external validity of the study, facilitating translation to other clinical settings.

### Ethical Considerations

The Regional Research Ethics Committee in Linköping (No 2016/484-31; 2017/512-32; 2018/147-32) has approved this study. For confidentiality, all communications and registrations of data in ePATH are transmitted through secure connections: Mobile BankID for patients and SITHS-login for care providers. All questionnaire and interview data will be anonymous and stored in accordance with the European Union legislation General Data Protection Regulation. Only the researchers will have access to data. Log data from the ePATH app will be stored in encrypted servers at Linnaeus University. Super administrators who have been responsible for the development and updates of ePATH will have access to the coding files of the app.

### Potential Harms

Criticism may be directed at the contact nurses if there are problems in the functioning and operability of ePATH. To avoid this situation, it will not only be emphasized that this is a research project where the views of the patients are valuable to improve ePATH but also that the contact nurses are merely users of the same eHealth tool: they are not responsible for it. If patients have criticisms, these should be addressed to the researchers. The intervention is unlikely to cause any harm to the participants, but there is a risk that patients may feel lost or deserted when the study ends. Therefore, ePATH will remain open for the intervention group patients to use after the 12 months have passed.

**Table 2 table2:** Template for Intervention Description and Replication checklist for the electronic Patient Activation in Treatment at Home intervention.

TIDieR^a^ item	Description
1. Brief name	ePATH^b^
2. Why	To compare the effectiveness of a tailored eHealth^c^ intervention (ePATH) on the basis of self-determination theory with standard care. Primary outcome is postoperative symptoms in men undergoing radical prostatectomy. Secondary outcomes are patient activation, motivation, overall well-being, and health literacy over time in and between groups.
3. What materials	User manual (paper) and Web-based mobile app for both patients and health care staff (only available in Swedish).
4. What procedure	During use of ePATH, interactions with health care staff and registration of self-care activities are carried out on an individual basis.
5. Who provided	The intervention was developed as a codesign project with health care researchers, technicians, patients, and health care staff. Researchers with theoretical knowledge of self-determination theory and backgrounds in social and behavioral science, cancer care, and as registered nurses will provide the contact nurses with a training session of approximately 2½ hours. One such session will be held at each study clinic and include how to log in to and use ePATH, how to add targeted information, and how to communicate through the app. All study sites will receive a manual with a written, supplementary tutorial to ePATH, information about the study, the cornerstones of the intervention, the process of enrollment, and a checklist over the contact nurses’ responsibilities regarding enrollment and collecting data from the medical records of participants. The contact nurses also get to practice hands-on during introductory sessions. To ensure the patient’s ability to perform the intervention, that is, self-care activities, patients are provided with a user manual for ePATH, and the contact nurses will contact all patients in the intervention group to make sure that they can log in to ePATH.
6. How	Delivery of the intervention takes place on an individual basis, depending on the patients’ needs. The patients start using ePATH approximately 1 to 2 weeks before surgery, depending on how soon they get their surgery scheduled.
7. Where	On the Web and mobile phone in patient homes.
8. When and how much	The intervention is based on self-care activities and engagement of the patients in their own homes. The enactment of the intervention is monitored through ratings in the app, communication, and follow-up questionnaires. The patients themselves decide to what extent they wish to use ePATH.
9. Tailoring	Contact nurses, in their close communication with each patient, have the possibility to add self-care packages that are relevant for the individual. These packages can be changed and tailored over time.
10. Modification	Researchers have close communication with the contact nurses about adaptions, to facilitate the use of ePATH in the clinical reality. All adaptions and modifications (what, when, and why) are thoroughly documented by the researchers.
11. How well (planned)	Step-by-step inclusion documents have been developed together with each clinic to suit its routines. Inclusion of patients is followed continuously by the research team and there is an ongoing dialogue with the contact nurses about possible difficulties.
12. How well (actual)	Adherence by the patients (how well was the intervention received?), that is, how many performed the suggested self-care activities, how often and how long, is investigated through log data and individual interviews. Dropouts will be described in detail.

^a^TIDieR: Template for Intervention Description and Replication.

^b^ePATH: electronic Patient Activation in Treatment at Home.

^c^eHealth: electronic health.

### Data Management

The researchers are not involved in any of the care provided before, during, or after surgery. Documents and digital data will be stored in accordance with Swedish legislation on how to file research data, the Archives Act (Arkivlagen, SFS 1990:782). All data will be reported at a group level.

## Results

This project is supported by the Kamprad Family Foundation of Entrepreneurship Research and Charity (grant number 2015-0067), the Swedish Cancer Society (grant number CAN 2017/748), the Cancer Foundation in Kalmar County, and the Medical Research Council of Southeast Sweden (grant numbers FORSS-657211; FORSS-760131).

Recruitment started in January 2018 and is expected to be completed by August 2019. Data collection will be completed in August 2020. The first results from this trial are anticipated to be published in January 2020.

## Discussion

This project addresses the posttreatment challenges of prostate cancer, which create special requirements on customized rehabilitation and psychosocial support. Many RP patients suffer from poor quality of life because of postoperative complications. Erectile dysfunction and urinary leaks are common and may be difficult to talk about openly. With the number of men living with cancer expected to increase, major attention needs to be paid to rehabilitation and psychosocial care as well as the creation of tools to help patients return to as normal a life as possible. ePATH for those living with prostate cancer, their families, and health care professionals provides access to a digital tool that can provide individualized information, be a communication link, and support self-care and empowerment during the course of care and treatment. The project will also increase the knowledge of how patients can be supported in performing self-care and feeling involved in their own care. If the anticipated effects of ePATH are found, this could imply significantly improved health outcomes for individuals and may also facilitate follow-up for health care professionals.

## Abbreviations

eHealth: electronic health
ePATH: electronic Patient Activation in Treatment at Home
mHealth: mobile health
PAM-13: Patient Activation Measure-13
PDE5Is: phosphodiesterase-5 inhibitors
PFMT: pelvic floor muscle training
RAND: Research ANd Development, a non-profit corporation in the USA
RP: radical prostatectomy
SITHS: an e-legitimation through WebTrust Certificate Authority
UI: urinary incontinence
